### Long-term decision analytical modelling

Next to the trial-based EE, a model-based EE will be performed, as it is expected that the economic impact of motherfit is best investigated by means of a long-term decision analytical model. First a structure and working model will be created that will facilitate the necessary analysis to be performed throughout the project. This model will be able to incorporate the values of all input parameters (both point estimates and uncertainty). Once the structure of the model is established, four essential types of data will be required: probabilities, costs, survival and health utilities (QALYs). Short-term costs and effectiveness data are readily available from the trial-based EE, whereas longer-term data may require synthesis of available evidence in the literature. Estimates of the economic impact will first be made using fixed estimates of probabilities, costs and health outcomes. Subsequently, a probabilistic sensitivity analysis will be performed which will address the joint uncertainty of the model inputs. As for the trial-based cost-effectiveness analysis, cost-effectiveness acceptability curves will be constructed. As with the trial-based EE, the model-based EE will address the cost per QALY (societal perspective) and cost per UI prevented (health care perspective). We will express uncertainty by means of confidence intervals and by creating cost-effectiveness acceptability curves. The appropriate time horizon will be agreed upon during the study but is expected to be lifetime.

### Budget Impact Analysis (BIA)

A BIA will be performed according to the International Society for Pharmacoeconomics and Outcomes Research (ISPOR) guidelines [48]. The BIA addresses the financial stream of consequences related to the implementation of motherfit group therapy and thus its affordability. The budget impact will depend, e.g. on patient acceptability of the programme, the uptake of the programme by health care professional and the target group, the cost-increase due to increased implementation of motherfit group therapy, and the cost savings due to preventing or reducing UI, i.e. reduced cost-of-illness. The structure and some data input of the decision analytical model developed for the EE will be adapted for the BIA. Input parameters will be based on results of the trial, national prevalence data, unit prices and tariffs obtained in the trial-based EE, and from the available literature when necessary. The analyses will be performed from different perspectives, including a health care budgetary perspective and a health insurers’ perspective. The model will take changes in the adoption/implementation of the programme, and patient acceptability/uptake into account and will compare different scenarios as regards to the swiftness and extensiveness of the uptake. In order to test the robustness of the results, sensitivity analyses will be performed. The time horizon will be varied from 1 year up to 5 years. No discounting will be applied.

### Withdrawal of individual subjects

Subjects can leave the study at any time and for any reason, if they wish to do so, without any consequences. The investigator can decide to withdraw a subject from the study for urgent medical reasons.

All women enrolled in the study will be followed and accounted for. Women who are unwilling or unable to commit themselves to the study plan and follow-up schedule (i.e. serious illness, during pregnancy, e.g. premature rupture of membranes, blood loss, severe high blood pressure, pre-eclampsia, movement out of the local area, etc.) may be withdrawn from the study. Women who will become pregnant again during the follow-up period of 18 months will be handled as dropout cases. Upon withdrawal of a subject, all documentation is available immediately for the investigators through the electronic case report file.

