### Blinding

Due to the nature of the interventions, the participants and PPTs cannot be blinded. During the trial the coordinating researcher is not blinded. However, once the participant has completed the questionnaires, it is not possible to make changes in the data due to locking of the questionnaires. Moreover, before the statistical analyses all participants will be appointed a new study number for which the coordinating researcher is blinded. Therefore, analyses will be done blinded for treatment allocation.

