### Interventions

#### Care-as-usual

In case participants with SUI are allocated to the CAU group, participating case managers give their normal advice and women make their own choices as to whether they want to participate in any kind of pregnancy-related course, visit to a physician or therapist.

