#### Motherfit group therapy

All women allocated to motherfit group therapy, and unaware or unable to contract their PFMs correctly, will be referred to the PPT for individual instruction before joining the motherfit group therapy (Fig. 3). Every participating region has a PPT who provides individual or group therapy. Motherfit consists of eight group therapy sessions of 60 min each, instructed and supervised by a registered PPT. In each group a maximum of four women are allowed to participate. Women of both studies can start when they have been randomised to motherfit group therapy. Therefore, the participant’s group composition may change over time. Motherfit includes instructions on pelvic floor anatomy and how to contract, relax and train the PFMs correctly and is combined with general physical exercises with a strong focus on self-management.

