### Data collection and outcome measures

All data (electronic case report forms and questionnaires at baseline and follow-up) of the participants and case managers will be collected in a (web-based) digital central database. Demographic variables and personal characteristics will be registered by the Nederlandse Vereniging voor Obstetrie & Gynaecologie vragenlijst (NVOG-q) at baseline for MOTHERFIT1 and MOTHERFIT2.

MOTHERFIT1: data will be collected at baseline, 34 weeks of gestation, 6 weeks and 6 and 18 months post-partum.

MOTHERFIT2: data will be collected at baseline and 4, 9 and 18 months post-partum.

The case manager fills in a first survey after the inclusion of a participant. For MOTHERFIT1 these questions include, among others, expected delivery date and current medication use. Two weeks after delivery, case managers receive a second survey regarding delivery variables. For MOTHERFIT2 the case manager fills in identical surveys, except the question on expected delivery date.

Participants in the intervention group fill in a training diary and three questions regarding their general physical activity level, weekly. The PPTs will register attendance of the participant during the intervention period and send it by postal mail to the researcher.

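### The withdrawal rule takes women out of the study rather than only out of the sessions, against the promise to follow everyone, and may bias the 18-month comparison

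*Protocol article*

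**What the plan says.** All statements are in the protocol article.

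- **Withdrawal of individual subjects.** "All women enrolled in the study will be followed and accounted for". The next sentence concerns "Women who are unwilling or unable to commit themselves to the study plan and follow-up schedule". Its bracketed list opens with serious illness and obstetric complications and ends: "severe high blood pressure, pre-eclampsia, movement out of the local area, etc.) may be withdrawn from the study". A separate sentence reads: "The investigator can decide to withdraw a subject from the study for urgent medical reasons".
- **Motherfit group therapy.** "Motherfit consists of eight group therapy sessions of 60 min each, instructed and supervised by a registered PPT". The training app with its push notifications is described in the same section.
- **Data collection and outcome measures.** "Participants in the intervention group fill in a training diary and three questions regarding their general physical activity level, weekly". Therapists record attendance and send it to the researcher. Questionnaires in both arms go into a web-based database.
- **Care-as-usual.** Case managers give their normal advice and "women make their own choices as to whether they want to participate in any kind of pregnancy-related course" or see a physician or therapist.
- **Blinding.** "During the trial the coordinating researcher is not blinded".
- **Statistical analysis.** Intention to treat, with multiple imputation as the preferred method for missing values.
- **Analysis of main hypotheses.** Listwise deletion in all the linear regression models.

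**The concern.** The rule does not distinguish a woman who stops the group sessions from one who stops giving outcome data. Both can be removed from the study. That contradicts the sentence before it, and it undermines the intention-to-treat analysis, which needs 18-month outcomes from all randomised women as far as they can be obtained.

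The loss is largely avoidable. The primary outcome is the ICIQ-UI-SF, a short self-report collected electronically. A woman who has moved, or whose pregnancy became complicated, will often still be able to complete it.

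The loss may also be uneven. For a motherfit woman, the plan she must commit to includes eight sessions, home training and a weekly diary. For a care-as-usual woman it is essentially the questionnaires. With an open-ended list of grounds and open allocation, more women may be removed from motherfit than from care-as-usual. If those women benefit less, the women who remain make motherfit look better than it is in all randomised women.

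**Working it through.** **1. The passages side by side.**

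| Section | Consequence for a woman who cannot keep to the plan |
|---|---|
| Withdrawal, follow-up sentence | She is followed |
| Withdrawal, next sentence | She can be removed from the study |
| Statistical analysis | She counts in the arm to which she was randomised |
| Analysis of main hypotheses | Without later data, she is deleted from the regression |

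The first and third rows cannot be fully honoured if the second and fourth are applied.

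**2. The plan's own figures (Sample size calculation, MOTHERFIT1).** Expected 18-month means are 8 (care-as-usual) and 5 (motherfit), so the difference is 3. With SD 5, two-sided alpha 0.05 and 90% power, the normal formula gives n = 2 × (1.960 + 1.282)² × 5² / 3² ≈ 58.4, so 59 per arm. The t-test version gives 60, as stated, and 60 / 0.8 = 75 per arm, also as stated. The planned difference of 3.0 is therefore a sound base for the illustration.

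**3. General form of the bias.** Let a share x of motherfit women be removed, with an 18-month mean d points worse than the motherfit women who stay. Let y and e be the same quantities for care-as-usual. Then

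observed difference = true difference + x·d − y·e.

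The bias is zero if d = e = 0. It also cancels if x·d = y·e, and it changes sign if removed motherfit women do better (d < 0, with y·e = 0).

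**4. One illustration.** Assumptions that are not in the documents: y = 0, and removed motherfit women have the care-as-usual mean of 8. Let m be the mean of the motherfit women who stay:

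(1 − x)·m + 8x = 5, so 8 − m = 3 / (1 − x).

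| x | m | Observed difference | Excess over 3.0 |
|---|---|---|---|
| 10% | 4.67 | 3.33 | 11% |
| 15% | 4.47 | 3.53 | 18% |
| 20% | 4.25 | 3.75 | 25% |

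**5. With no true effect.** Take d = 3, y = 0, SD 5, and 75 care-as-usual women against 75(1 − x) motherfit women. The shift is 3x.

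- x = 10%: shift 0.30, standard error 5 × √(1/75 + 1/67.5) = 0.839, two-sided type I error about 6.5%.
- x = 20%: shift 0.60, standard error 5 × √(1/75 + 1/60) = 0.866, two-sided type I error about 10.7%.

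With d = 0 it stays at 5%. With d = −3 the shift has the same size in the other direction.

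**The case against.** The strongest reply is that the text does not describe the removal of poor attenders from one arm. Most of this stands.

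- A reader might infer that missed sessions or an unkept diary are grounds for removal. They are not listed; the named grounds are illness, obstetric complications and relocation. Non-attendance enters only through the reference to the study plan and the open end of the list. The economic evaluation plans a comparison of adherent and non-adherent women, which presupposes that non-adherent women stay in the data.
- A reader might infer that an unblinded investigator decides. The sentence names no decision-maker. The investigator's stated power covers urgent medical reasons only, and the Blinding section gives the coordinating researcher no power to withdraw anyone.
- A reader might infer that only motherfit women can be lost. Care-as-usual women can also fail the follow-up schedule, fall ill or move. The eligibility criteria also screen both arms for motivation, for refusal of the app and for expected loss to follow-up.
- A reader might infer that the effect is inflated whatever missing-data method is used. Size and direction rest on assumptions. Multiple imputation, informed by earlier scores and attendance, could reduce a bias.
- The 20% dropout allowance applies to each arm and must also cover other losses such as a new pregnancy, so 20% from this rule in one arm is an extreme case.

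It can also be said that a journal article leaves such detail to the full protocol. That does not answer the point. The article states a removal rule, and the rule conflicts with its neighbouring sentence and with the stated analysis principle.

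**Conclusion.** The point holds as a contradiction with a possible bias, not as a demonstrated inflation. The rule allows removal from the study on grounds that mostly do not prevent outcome collection, against the undertaking to follow all women and against intention to treat. Listwise deletion then carries those removals into the regression on the ICIQ-UI-SF.

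That removals fall more heavily on motherfit is plausible, because the treatment burden lies there and allocation is open, but the documents do not establish it. A bias towards motherfit is the likelier direction if removed women benefit less. The Discussion supports this in part, since it treats adherence as strongly predictive of lasting results. The figures of 3.33 to 3.75 points against 3.0 rest on an assumed removal of 10% to 20% from one arm, no benefit in the women removed, and a completers-only estimate. They show what the rule could do, not what it will do. The change is worth making because it is cheap and protects the primary comparison.

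**What to change.** Reword the section on withdrawal so that it defines two states, applied equally in both arms:

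1. **Stopped motherfit** (arises in the motherfit arm only). Record the date and reason. The woman stays in the study and receives every remaining scheduled questionnaire up to 18 months, including the ICIQ-UI-SF, EQ-5D-5L and cost items.
2. **Withdrawn from follow-up.** Used only when the woman herself declines further questionnaires or withdraws consent.

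Remove non-commitment to the study plan and moving away as grounds for ending data collection. Report both states by arm, with reasons. Reconcile the withdrawal section with the intention-to-treat and multiple-imputation statement and with the listwise-deletion sentence, so that one approach governs women with incomplete data. Clinical decisions to stop exercise are unaffected.

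The cost is a wording change and some extra reminders. The questionnaires and their schedule already exist, and recruitment was still under way when the article appeared, so later outcomes could still be collected.

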## Discussion

The two motherfit studies are studies aim to evaluate whether motherfit group therapy is (cost-)effective 18 months post-partum for pregnant (MOTHERFIT1) and post-partum women (MOTHERFIT2) with SUI. As health care costs are rising in general, there is a need for cost-effective strategies, which is one of the main reasons for initiating the motherfit studies. The motherfit studies are, to our knowledge, the first studies that evaluate both longer-term results and health care costs compared to CAU in pregnant and post-partum women with SUI. The endpoint of 18 months post-partum is chosen because of the increasing possibility of a subsequent pregnancy and consequently loss to follow-up. In order to sustain long-term results, it is known that adherence is a strong predictive factor [33]. Therefore, motherfit group therapy not only focusses on PFMT, general fitness exercises and education, but also has a strong emphasis on adherence and self-management. Adherence to PFMT will be supported by a mApp.

Currently, no guidelines on urinary incontinence exist specifically for pregnant and post-partum women. In case motherfit demonstrates to be (cost-)effective, implementation of motherfit group therapy should be considered in peri-partum care and future guidelines.

## Trial status

Participants for the MOTHERFIT1 and MOTHERFIT2 studies are currently being recruited in five regions in the southern part of The Netherlands. The first patient was randomised on 4 October 2017. Last participant follow-up for MOTHERFIT1 and MOTHERFIT2 is expected in August 2020; version 5, 31 March 2017. The trial registration number is NTR5971 (Dutch Trial Register), 18 July 2016.

## Abbreviations

BIA: Budget Impact Analysis
CAU: Care-as-usual
CTCM: Clinical Trial Center Maastricht,
EE: Economic evaluation
GEE: Patient Global Impression of Severity
ICIQ-UI-SF: International Consultation on Incontinence Questionnaire-Short Form
IIQ-7: Incontinence Impact Questionnaire
ISPOR: International Society For Pharmacoeconomics and Outcomes Research
LOCF: Last observation carried forward
mApp: Mobile app
NVOQ-q: Nederlandse Vereniging voor Obstetrie & Gynaecologie vragenlijst
PFM(T): Pelvic-floor-muscle (training)
PFMGT: Pelvic-floor-muscle group therapy
PPT: Pelvic physiotherapist
QALY: Quality-adjusted life-year
QoL: Quality of life
RCT: Randomised controlled trial
(S)UI: (Stress) urinary incontinence
WHO: World Health Organisation
